### Bias reduction and manipulation check

A manipulation check will be performed assessing any doubts or suspicions concerning the treatment allocation or the cover story. Preliminary data indicates that the cover story, including the group allocation, are considered convincing by the participants: 18 of 19 people answered “no” to a post-experimental question asking “Did you at any point find the experimental instructions unconvincing?”.

Allocation to the experimental groups will happen in a room adjacent to the room where the pain measurement takes place, and without insight of the laboratory assistant into the allocation. He or she will therefore be fully blinded to the treatment allocation when performing the retest. Measures will be taken to ensure that allocation is not revealed by the participant: The participant will be asked by the VEx, HEx or audio/text display not to notify the laboratory assistant of their treatment allocation, and the laboratory assistant will document any deviations. Audiovisual recording of the participant/laboratory assistant-interaction will be considered if necessary.

All measurements (except blood pressure and skin temperature) and pain reports will be performed on a computer without communication with the laboratory assistant. Furthermore, the instructions for the continuous pain ratings contain a line to emphasize participant anonymity and non-involvement of the laboratory assistant in data analysis, “This next part is very important: Your ratings will be analyzed by a blinded experimenter only after the session is over. Focus as much as possible on the sensation in your immersed hand, and feel totally free to rate your pain precisely and truthfully. Try not to let my presence or any other thought affect the way you report the sensation, or affect the number of trials you complete.” Also, during the pain measurement, the laboratory assistant will remove himself or herself from the immediate vicinity of the participant to sit down at a table in the participant's field of view, but facing in the same direction as the participant as to not give the participant the feeling of being observed (beyond an initial making sure that all instructions are complied with).

Some extent of selection bias is expected, as an aversive stimulation is employed. While a monetary compensation of $20 is offered for the ca. 2 h experiment, pain sensitive people will be potentially underrepresented in the sample. Systematic deviations from the norm will be assessed by analyzing questionnaire data (specifically, reported pain sensitivity via the PSQ) and actual responding to the stimulus. Preliminary data does not suggest that this is a serious issue, with roughly normally distributed pain sensitivity (data not shown).

### Analysis and sample size estimation

Data entry is almost fully automated via the touch-screen interface (for continuous pain ratings), a digital survey tool (for other pain ratings and psychological measurements), and on-line registration of physiological parameters. The exception are blood pressure and temperature data which are documented on a score sheet. Continuous pain ratings will be recorded at a sampling rate of ca. 40 Hz, but downsampled to 1 s means for analysis.

Data will be analyzed with hierarchical linear modelling (HLM). Among other strengths, this approach enables us to consider both categorical and continuous predictor variables (e.g., covariates), and the inclusion of cases with missing values, allowing for the number of repeated measures to differ across persons [40]. HLM puts no constraints on the number of repeated measurements, which permits an analysis of differences in the time course of pain. HLM also allows for considering random effects (intercepts and slopes), suitable to the high interindividual variability of pain sensitivity [41].

The robustness of results will be assessed by outlier analyses of the regressional models provided by HLM, including contrasting of predicted versus actual values, studentized residuals and Mahalanobis’ distance. Outliers will be excluded both at the within-person level (individual measurement occasions) and the between-person level (exclusion of individuals with outliers). Robustness will be gauged by changes in the significance of the results.

HLM sample size estimation considers the sample size at level 1 (*n*; in our case, the repeated measurements within-persons) and the sample size at level 2 (*N*; in our case, the individual participants). Recommendations vary (e.g. [42, 43]); Hox [43] suggests larger sample sizes of *n* = 20 and *N* = 50 when investigating cross-level interactions. The wealth of data points provided by the second-by-second continuous pain ratings easily allow for meeting the *n* = 20 suggestion. However, while a total of 600 s of immersions will be available, the effective sample size will be lower due to large intraclass correlations, or strong autocorrelation. Due to the high interindividual variation of pain sensitivity, we would nevertheless aim for including *N* = 50 individual participants to determine difference between the six groups. Estimating 15 % attrition, the projected sample size therefore amounts to *N* = 58 individuals.

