### Procedure

Participants will continually rate their pain during Sequence 1 under supervision of a laboratory assistant. They will then be randomly assigned to one of the 3(Metaphor)*x*2(Instruction) experimental groups. In a separate room, they will interact with the Metaphors delivering the Instructions. For the VEx and audio/text condition, interactional components are displayed in Fig. 2b. Crucially, neither assignment will be revealed to the laboratory assistant.

During the placebo manipulation, the inert medication will be automatically dispensed using a self-constructed pill dispenser controlled by an Arduino platform (https://www.arduino.cc/). For VEx and audio/text condition, pill dispension will be performed by the presentation software; in the HEx condition by pressing a button.

An overall inter-Sequence interval of 35 min will be observed for cutaneous sensitivity to recover, and to provide a plausible cover story for the medication to take effect (in the “medication” instruction).

The pain change at retest, compared between experimental groups, will be the main outcome.

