### Hypotheses and expected results

The PE would be constituted by a larger symptom improvement from Sequence 1 to Sequence 2 in the “medication” Instruction, than in the “control/placebo” Instruction (“medication”(S2-S1)>“control”(S2-S1). This is a general test of the efficacy of the placebo paradigm, which is a crucial building block for assessing the effect of the different Metaphors.

The design does not strictly permit the establishment of equivalence between Metaphors in the sense of a non-inferiority trial, which is deemed too ambitious at this stage. For the proposed protocol, a non-significant difference between VEx and HEx would be considered as a first step to establish the viability of the VEx (HEx = VEx). On a descriptive level, we are expecting a slightly lower effect induced by the VEx, but lower variance than under the HEx, amounting to comparable effect sizes. Beyond that, it is hypothesized that the audio/text Metaphor induces a smaller symptom improvement than the other conditions (HEx = VEx > audio/text) due to absence of visual social cues.

Using a more fine grained analysis at the Trial level could yield additional information, such that groups differ in early or late Trials only, or that the slope (pain changes in consecutive Trials) is different between groups. For example, a significant difference between “medication” vs. “control” could come about by a shallower pain increase in consecutive Trials in Sequence 2, despite identical initial sensitivity (see Fig. 4).

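### Outlier-excluded results are to be judged only by whether significance changes, and the plan does not say that the full-data fit carries the inference

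*Protocol article*

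**What the plan says.** The relevant paragraph is in Analysis and sample size estimation. It opens with its purpose: "The robustness of results will be assessed by outlier analyses of the regressional models provided by HLM", with the diagnostics listed as "including contrasting of predicted versus actual values, studentized residuals and Mahalanobis’ distance". The exclusion sentence follows and carries no condition: "Outliers will be excluded both at the within-person level (individual measurement occasions) and the between-person level (exclusion of individuals with outliers"). The paragraph closes with its only criterion: "Robustness will be gauged by changes in the significance of the results".

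The results to which this applies are defined elsewhere. Procedure states: "The pain change at retest, compared between experimental groups, will be the main outcome". Hypotheses and expected results gives the main contrast: "The PE would be constituted by a larger symptom improvement from Sequence 1 to Sequence 2 in the “medication” Instruction", compared with the control Instruction. The same section treats a non-significant VEx–HEx difference as a first step towards showing that the VEx is viable. It adds that the team will move on to more complex protocols if no significant difference is found.

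**The concern.** Two things are fixed badly in the stated text.

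First, robustness is reduced to one binary question: does significance change? A p-value near the threshold can cross it when the estimate hardly moves. A p-value far from the threshold can stay on its side when the estimate moves a good deal. The second case matters here because the article acts on non-significance for VEx versus HEx. A finding that remains non-significant after exclusion would be recorded as stable, whatever had happened to the size of the difference.

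Second, exclusion is stated as something that will be done, but the article never says that the full-data model is the one to be reported. Studentized residuals and predicted-versus-actual contrasts are computed from the outcome and the fitted model. Removing poorly fitted people shrinks the residual variance, and a test on the remaining data takes that smaller variance at face value. If that test carried the inference, the placebo-effect test would not hold its nominal level. With about 8 people per cell, each removal also weighs heavily on the estimate.

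**Working it through.** **The plan's own figure.** The only computed design figure is the projected sample size of 58. 50 × 1.15 = 57.5, rounded up to 58, reproduces it; 50 / (1 − 0.15) = 58.8 would give 59. The one-person difference has no bearing on this point.

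**Inputs from the article.**
- 50 participants in six groups: 50/6 ≈ 8.3 per cell and 25 per Instruction level (Analysis and sample size estimation).
- SD of continuous ratings 15.0 in Sequence 1 and 15.5 in Sequence 2; intraclass correlation .72 (Pilot study 2).

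**Assumptions, not in the article.** The intraclass correlation is used as the between-Sequence correlation. The test is two-sided at 5%. A person is excluded when the absolute externally studentized residual reaches 2, 2.5 or 3. Errors are normal, t with 3 df, or skewed (chi-square with 3 df). The model is a person-level comparison of change scores. It simplifies the planned HLM and leaves out exclusion of single occasions and Mahalanobis' distance.

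**Step 1. SD of change.** √(15.0² + 15.5² − 2 × 0.72 × 15.0 × 15.5) = √130.45 = 11.42 VAS points.

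**Step 2. Borderline effect, 25 vs 25.** 1.96 × 11.42 × √(4/50) = 6.33 VAS points. Simulated power at this effect is 49%; at 6.5 points it is 50%.

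**Step 3. How often exclusion flips significance when there are no true outliers.** Normal data, 20,000 trials per setting for the two-group fit and 8,000 for a six-cell fit:

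| Cut-off | Mean removed of 50 | Flips at 6.33 points | Flips at 6.5 points | Flips, six-cell fit, 50% power | Flips, no effect |
|---|---|---|---|---|---|
| 2 | 2.6 | 15.1% | 15.7% | 15.8% | 8.0% |
| 2.5 | 0.8 | 9.0% | 9.5% | 9.8% | 4.3% |
| 3 | 0.2 | 3.2% | 3.3% | 3.6% | 1.5% |

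The flip-rate columns other than the last come from trials with a true effect; the last has none.

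**Step 4. Type I error by which fit is reported.** 20,000 trials per setting, no true effect, nominal 5%:

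| Reported fit | Normal | t, 3 df | Skewed |
|---|---|---|---|
| Full data | 5.0% | 4.7% | 5.0% |
| Excluded, cut-off 2 | 11.6% | 8.5% | 7.9% |
| Excluded, cut-off 2.5 | 7.9% | 7.0% | 7.1% |
| Excluded, cut-off 3 | 6.1% | 6.3% | 6.4% |

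A six-cell fit with normal errors gives 12.1%, 8.2% and 6.3% for the excluded-data rows. If either fit may be claimed, the two-group figures with normal errors are 12.3%, 8.6% and 6.3%.

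**Step 5. The VEx–HEx contrast.** The difference between the two placebo effects uses four cells. Its standard error is 11.42 × √(4/8.33) = 7.9, so with a normal quantile it is non-significant anywhere within about ±1.96 × 7.9 = ±15.5 VAS points. Removing one person who lies 2 SD (22.8 points) from the mean of a cell of 8 moves that cell mean by 22.8/7 = 3.3 points, and moves the VEx–HEx difference by the same amount. A shift of that size can easily leave the result non-significant, and the stated criterion would then report no change.

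**The case against.** The strongest reply is that this is already a sensitivity analysis. The paragraph opens and closes on robustness, a change in significance requires two fits, and the preceding paragraph describes the main HLM with no exclusion step. That largely stands. A reader might infer from the unconditional exclusion sentence that the trial's type I error is inflated. The documents do not support that as a flat statement: nothing makes the excluded-data fit primary, and Step 4 shows no inflation when the full-data fit is. What remains is that the article leaves the question open.

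Two other strong readings should also be set aside. One is that exclusions are decided unblinded. The article does not say so; under Bias reduction and manipulation check, participants are told that a blinded experimenter will analyse their ratings. The other is that one extreme second among 600 would remove a whole person. The sentence separates occasions from persons. A chance of 1 − (1 − 0.0027)^600 = 80% needs independent ratings, whereas the article itself expects strong autocorrelation. With an assumed 10 to 50 effective ratings the chance is about 3–13%.

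It can also be said that flips are most frequent near 50% power, that stricter cut-offs remove fewer than one person on average, and that a sensitivity analysis ought to reveal a flip. The first two are correct, and the tables show it. The third does not rescue the criterion, because the flips in Step 3 occur in clean data and so say nothing about outliers. The absence of stated cut-offs is not held against the article, since they may sit in a fuller plan. The article also concedes that it cannot establish equivalence of VEx and HEx, but it still bases its next step on non-significance.

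**Conclusion.** The point holds in a limited form, at minor to moderate severity. On any reading, change in significance is a poor sole measure of robustness. Near 50% power it flips in about 16%, 10% and 3–4% of trials with no real outliers, at assumed cut-offs of 2, 2.5 and 3, and it can miss a material shift in the VEx–HEx estimate. Type I error of about 12%, 8% and 6% (normal errors) arises only if the outlier-excluded fit is the one reported; with the full-data fit as primary it stays at 5%. These sizes rest on assumed cut-offs and on a person-level simplification of the HLM, with the pilot intraclass correlation used as the correlation between Sequences.

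**What to change.** In Analysis and sample size estimation, state three things:

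1. The primary analysis uses all randomised participants with consented data and all valid ratings.
2. The outlier-excluded fit is a sensitivity analysis only.
3. Robustness is judged by the change in the placebo-effect estimate and the VEx–HEx estimate, each with its 95% confidence interval in VAS points, and not by a change in significance.

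The cost is about two sentences of wording, one extra reported comparison, and possibly a slightly wider primary confidence interval.

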### Design

The study will follow a partially blinded, deceptive, repeated measures design. Participants will undergo a baseline pain measurement (five 60 s immersions of the hand in hot water; see “Pain protocol”), followed by treatment with a supposed pain killer, and a retest pain measurement. In this design, every participant will only receive an oral placebo (no active medication), but groups will differ as to the instruction about the (actually inert) “medication’s” efficacy.

Within-persons and between-persons predictors include■ the mode of treatment/instruction presentation (between-persons predictor Metaphor, 3 levels: HEx, VEx, text/audio)■ the instruction itself (between-persons predictor Instruction, 2 levels: “medication” (deceptive) vs. “inert” (truthful)); this manipulation is double-blind to both participant and laboratory assistant■ the pain measurement repetition, which constitutes nested within-persons predictors (immersion Time nested in immersion Trials nested in immersion Sequences). In the scope of this study outline, we will only address Trials and Sequences pertaining to the expected results.

See Fig. 2a for a design and protocol outline. Within-persons and between-persons predictors correspond to level 1 and level 2 variables used in hierarchical linear modelling nomenclature (see “Analysis and sample size estimation”).

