### Pilot study 2: evaluation of the pain protocol

To characterize the pain protocol (see above) and estimate reproducibility across Sequences (including possible carry-over effects like habituation and sensitization), we conducted a pilot study with only a waiting period between the two Sequences. All means are provided with standard deviations; significance testing was performed with hierarchical linear model analysis, cf. “Analysis and sample size estimation” (a more in-depth discussion is beyond the scope of this article). In this study, we included 33 healthy participants (21 female, 12 male; age 20.1 ± 2.4). Continuous pain ratings almost invariably increased within Sequences/between Trials. On average, participants showed substantial amounts of pain in both Sequence 1 (VAS 46.4 ± 15.0, range 23.5 to 83.6) and Sequence 2 (VAS 40.8 ± 15.5, range 18.8 to 78.8), with normal distributions on both occasions. These means constitute a slight but significant overall decrease in pain between the two Sequences. Conversely, single retrospective ratings show no difference for intensity (VAS 53.8 ± 17.7 versus 52.6 ± 21.1) and unpleasantness (VAS 55.9 ± 17.1 versus 55.6 ± 21.3).

The continuous ratings exhibited good reproducibility (intraclass correlation coefficient(2,1) *ρ* = .72) between the two Sequences, comparable to that of the retrospective ratings of intensity (*ρ* = .77) and unpleasantness (*ρ* = .68).

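### N = 50 comes from a generic multilevel rule and is said to separate six groups, but at about eight people per group it supports only the pooled Instruction contrast

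*Protocol article*

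**What the plan says.** All references are to the protocol article.

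- **Analysis and sample size estimation** cites a recommendation of n = 20 measurements and N = 50 persons "when investigating cross-level interactions". It says that the "second-by-second continuous pain ratings easily allow for meeting the" n = 20 figure, then concedes that "the effective sample size will be lower due to large intraclass correlations, or strong autocorrelation". It still aims for 50 "individual participants to determine difference between the six groups" and, with 15% attrition, projects 58. The section states no target effect, SD, alpha or power.
- **Design** makes Metaphor (three levels) and Instruction (two levels) between-persons predictors.
- **Procedure** defines the main outcome as the change in pain at retest, compared between groups.
- **Hypotheses and expected results** lists a pooled placebo effect (Instruction), no significant VEx-HEx difference, and a smaller improvement under audio/text. It expects the VEx effect to be slightly lower than the HEx effect. If no significant VEx-HEx difference is found, the programme proceeds; if the HEx is superior, the VEx returns to design.
- **Challenges** warns that the placebo effect may not be pronounced.

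**The concern.** A rule of thumb for cross-level interactions says nothing about how finely the persons are divided. Here they are divided into six groups, and every comparison of interest is between persons. Recording more seconds per immersion does not reduce the variation between people in how much their pain changes, and that variation limits each group comparison. The precision therefore depends on about eight people per group, and the paragraph never works out what that buys.

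What is at stake is the VEx-HEx comparison. The next stage of the programme depends on whether that difference is significant. If the design can hardly detect it, a non-significant result is the likely outcome whether or not the VEx elicits any placebo effect.

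**Working it through.** **The plan's own figure.** N = 50 equals the cited recommendation and cannot be rebuilt as a power calculation, because no effect, SD, alpha or power is given. The attrition step can be checked: 50 x 1.15 = 57.5, rounded to 58; 50 / 0.85 = 58.8, rounded to 59. The difference of one person is immaterial.

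**Inputs from pilot study 2 (33 people, no intervention).** Continuous ratings: SD 15.0 in Sequence 1, SD 15.5 in Sequence 2, means 46.4 and 40.8, ICC(2,1) .72. This ICC counts the 5.6-point mean shift as disagreement; with the shift removed, the correlation is about .76. I use r = .72 to .76.

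**Assumed, because not stated.** Two-sided alpha 0.05, 80% power, equal allocation (50 / 6 = 8.33 per group), residual df 50 - 6 = 44, no multiplicity adjustment.

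**SD of change** = sqrt(15.0² + 15.5² - 2r x 15.0 x 15.5)
- r = .72: sqrt(465.25 - 334.80) = 11.4
- r = .76: sqrt(465.25 - 353.40) = 10.6

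**Standard errors and detectable effects.** From the noncentral t with 44 df, the effect detectable with 80% power is 2.865 x SE. The 95% CI half-width is 2.015 x SE.

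| Contrast | SE | SE (VAS) | Detectable (VAS) | CI half-width (VAS) |
|---|---|---|---|---|
| Instruction, pooled (25 v 25) | SD x sqrt(4/50) | 2.99 to 3.23 | 8.6 to 9.3 | 6.0 to 6.5 |
| Placebo effect within one Metaphor (8.33 v 8.33) | SD x sqrt(2/8.33) | 5.18 to 5.60 | 14.8 to 16.0 | 10.4 to 11.3 |
| VEx-HEx difference in placebo effect | SD x sqrt(4/8.33) | 7.33 to 7.91 | 21.0 to 22.7 | 14.8 to 16.0 |

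In SD units the detectable effects are about 0.8, 1.4 and 2.0. The last, 21 to 23 points, is about half of the pilot's Sequence 2 mean of 40.8.

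The audio/text hypothesis, read as a difference in placebo effect between audio/text and the average of the other two Metaphors, has SE = SD x sqrt((2/8.33) x (1 + 1/4 + 1/4)) = 0.6 x SD, or 6.3 to 6.9. The detectable difference is about 18 to 20 points.

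**Power at N = 50 for an assumed 10-point placebo effect**
- Pooled Instruction effect: 0.86 to 0.91
- Placebo effect within one Metaphor: 0.42 to 0.47
- VEx-HEx difference if the VEx produces none of the effect: 0.23 to 0.27
- VEx-HEx difference if the VEx produces half of it (5 points): about 0.09 to 0.10

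So if the HEx produced 10 points and the VEx none, the comparison would still be non-significant in roughly three trials out of four (1 - 0.27 = 0.73; 1 - 0.23 = 0.77).

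**The case against.** The best defence has three parts. The article gives no target effect, so whether 50 is enough depends on what one assumes. It also discloses its limits: it concedes the autocorrelation, disclaims equivalence and non-inferiority, and calls a non-significant VEx-HEx difference only a first step. And Instruction by Sequence is itself a cross-level interaction, so the cited rule is not out of place for the pooled test.

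Much of this stands. The pooled Instruction test is reasonable for effects of about 9 points, and nothing has been concealed. But the article's own expectations, a placebo effect that may be weak and a VEx effect only slightly lower, lie far from a detectable difference of 21 to 23 points. The equivalence disclaimer does not change the rule that non-significance lets the programme proceed.

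Three stronger readings are tempting, and the documents do not support them.

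- **That n = 20 is not met.** This depends on a lag-1 autocorrelation that the article does not give. If the ten separate one-minute immersions are laid out in time under an assumed first-order autoregressive process, 20 independent values are reached up to a lag-1 correlation of about 0.952. In any case, n = 20 does not govern the group comparisons.
- **That the model will understate the standard error of Instruction by Sequence.** This would need a model with a random intercept only. The article describes ratings nested in Trials and Sequences and mentions both random intercepts and random slopes. The exact specification is detail that an article may leave to the full plan.
- **That the pilot's finding, "These means constitute a slight but significant overall decrease in pain between the two Sequences", shows such an understated error.** It does not. At person level, 5.6 / (SD / sqrt(33)) gives t = 2.8 to 3.0 and p = 0.005 to 0.008, so the decrease is significant without counting seconds.

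**Conclusion.** The concern holds for what N = 50 is said to achieve. The number supports one contrast, the pooled Instruction effect, at about 9 VAS points (0.8 SD). It does not give useful power to separate the six groups (15 to 16 points for a pair of Instruction groups within one Metaphor) or to compare the placebo effect between VEx and HEx (21 to 23 points).

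These figures rest on pilot study 2 and on the assumed alpha, power and equal allocation. The pilot had no intervention, so if people differ in placebo response the SD of change could be larger and the figures optimistic. Adjusting for baseline gains little: the residual SD is about 10.0 to 10.8, and the VEx-HEx detectable difference is still about 20 points or more.

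The trial can still be run at this size. What needs to change is the stated capability and the reading of a non-significant VEx-HEx result.

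**What to change.** Keep N = 50 analysed and revise the text:

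1. In the sample-size paragraph, replace the claim about six groups with what the number buys: the pooled Instruction contrast is the confirmatory test, with a detectable effect of about 9 VAS points at 80% power. State the SD of change, alpha and power used.
2. State that precision for group comparisons is set by the number of persons, not by the count of one-second ratings.
3. Report the within-Metaphor and VEx-HEx contrasts as estimates with 95% confidence intervals, giving the expected half-widths of about 10 to 11 and 15 to 16 points.
4. In the hypotheses section, base the VEx viability statement and the decision to proceed on that interval instead of on non-significance.

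It would also be sensible to confirm in the full analysis plan that the model includes a random Sequence slope for each person, or that the primary test uses person-level Sequence means. This is a point to confirm, not a shown error.

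The cost is text only, with no extra participants or measurements. The stated capability becomes less favourable, and a null VEx-HEx result will no longer support moving on by itself.
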